
### 2.9. Adverse Effects

Both treatments are considered safe and, in most cases, well tolerated by participants. Adverse events are defined as unwanted and involuntary signs, symptoms, or conditions that may occur following the intervention, regardless of whether there is a direct causal relationship with the treatment. To date, no significant risks associated with the intervention have been reported. Electroanalgesia is regarded as a low-risk technique. Although no significant adverse reactions have been reported, mild effects such as skin irritation or transient redness at the site of electrode placement or mild allergic reactions to the materials used may occur, which usually resolve without medical intervention. Regarding the exercises, these will be prescribed on an individualised basis following the patient’s assessment, thereby minimising the risk of side effects. Nevertheless, improper execution could cause transient muscular discomfort, which is generally mild and resolves spontaneously within 48 h. Mild muscle fatigue may also occur, which subsides with adequate rest.

All potential adverse effects will be recorded by the investigators. If they occur, the frequency of occurrence will be analysed between the intervention groups. Participants will also be informed of these possible effects during the informed consent process. They will have the option of contacting the research team, either by telephone or email, should they have any questions or experience any symptoms not related to the expected progression. Furthermore, regular reviews of safety protocols will be conducted to ensure the well-being and protection of all participants. In the event of severe adverse effects, the participant will be withdrawn from the study and referred to the pertinent medical unit. Due to the very low risk of severe adverse effects, the approval of the ethics committee, and the close supervision of the research team, the involvement of an external data monitoring committee was considered unnecessary.

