This study aims to analyse the cost-effectiveness and cost-utility of a self-administered telerehabilitation programme based on McKenzie cervical exercises and electroanalgesia compared with the same programme delivered face-to-face in patients with NSCNP. The main objectives are to (1) determine the average cost per patient associated with each intervention; and (2) calculate and report the incremental costs and benefits associated with the implementation of the intervention via telerehabilitation in comparison with the face-to-face intervention.

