The telerehabilitation programme will use a support system for the treatment of cervical pain based on web technologies, accredited as a healthcare website. This system has a structure based on four sections: database management, database user profiles, recommendations, and feedback/biofeedback procedures. This system allows for registering and entering a subject and modifying a treatment with electroanalgesia and exercises, according to the symptomatic evolution of the pain. It is based on an initial patient assessment system. Once the initial diagnosis of the patient is made according to the McKenzie clinical subtypes of NP, a multimedia database will be developed with examples of specific treatments (according to symptom evolution) for postural syndrome, dysfunction syndrome, and derangement syndrome. Patients will use their computer or mobile device connected to the internet to access the platform, where they will find the videos of the combined application of electroanalgesia and exercises. The treatments will be provided by the system. The database is configured to accommodate the application of electroanalgesia and exercises based on the diagnosis according to the McKenzie method. Each subgroup corresponds to a programme and a set of previously defined exercises with electroanalgesia as well as recommendations for daily activities, such as manual activity, sitting, standing, or ergonomic postures for daily activities. Therefore, each treatment will use a feature vector VT with 3 characteristics (one for each subgroup), where each position will contain a value indicating the degree of difficulty for each treatment subgroup. The system calculates and recalculates recommendations and updates the values of the relevance estimates for the recommended treatments. The system will recommend treatment Y for subject X, and depending on the modification or remission of the pain, at the start of each session, it will continue with the same plan or will be adjusted following the therapeutic algorithm of the McKenzie method. Once the treatment is completed, the outcome measures will be evaluated. This evaluation will be recorded in the system to be subsequently available in the recommendation processes. Furthermore, the system recalculates the evaluations provided by the patients. To facilitate the correct execution of the treatment, each element on the website is arranged in the order in which it should be performed and represented by icons that are easily associated with each step. This ensures that patients are guided intuitively as they scroll through the website. To verify attendance and ensure that patients complete all sessions properly, patients must enter their ID in the field provided on the website at the end of each session. This confirmation will be emailed automatically to the responsible clinician.

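### Adverse-effect frequency is to be compared between arms with no common solicited question described, while therapist contact differs by arm, so the comparison is open to differential ascertainment, probably favouring telerehabilitation

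*Protocol article*

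**What the plan says.** Section 2.9 (Adverse Effects) defines adverse events broadly, "regardless of whether there is a direct causal relationship with the treatment". It gives the duty to record them to the study team: "All potential adverse effects will be recorded by the investigators". It then commits to a comparison: "If they occur, the frequency of occurrence will be analysed between the intervention groups". The one reporting route it describes from the participant's side is optional: "They will have the option of contacting the research team, either by telephone or email, should they have any questions or experience any symptoms". That sentence covers participants in both arms, and it goes on to limit the symptoms to those outside the expected course. The effects the section anticipates are minor: skin irritation or transient redness under the electrodes, mild allergic reactions, mild muscle fatigue, and muscular discomfort "which is generally mild and resolves spontaneously within 48 h".

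Contact during treatment differs by design. The Introduction describes a "self-administered telerehabilitation programme based on McKenzie cervical exercises and electroanalgesia compared with the same programme delivered face-to-face". Under 2.4 (Interventions), both arms have 24 sessions, and experienced therapists deliver the control sessions in person. In the other arm the web system supplies the treatment, takes account of pain change at the start of each session, and verifies attendance at the end: "patients must enter their ID in the field provided on the website at the end of each session".

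Under 2.5 (Data Collection), both arms attend in person at baseline, 8 weeks and 6 months. The data listed there are demographic, clinical, resource-use, cost and sick-leave items. Table 2 has rows for demographic variables and the economic evaluation, and none for adverse effects.

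**The concern.** A comparison of adverse-effect frequencies is informative only if an event has about the same chance of being recorded in each arm. Here one arm has a therapist present up to 24 times in eight weeks and the other has none at the session. The formal reporting route is the same for both, but the control arm has an additional opportunity for events to be seen or mentioned.

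The type of event makes this matter. Redness under an electrode, or soreness that settles in two days, is easily noticed or mentioned at a session. It is unlikely to prompt a phone call or email, and will often be forgotten by an 8-week visit. The contact route is also narrower than the section's own definition: it invites reports of symptoms outside the expected course, while the definition includes any unwanted symptom whatever its cause.

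Section 2.9 itself links muscular discomfort to poor execution of the exercises. If that is more frequent without supervision, a true excess in telerehabilitation could be hidden. If the true rates are equal, telerehabilitation could appear safer. Either way, the reported contrast would partly reflect how events were found.

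**Working it through.** **1. What each described contact would capture**

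| Contact | Face-to-face | Telerehabilitation | Described as collecting adverse effects? |
|---|---|---|---|
| Optional phone or email (2.9) | yes | yes | yes, for symptoms outside the expected course |
| Therapist at up to 24 sessions (2.4) | yes | no | no; opportunity inferred from mode of delivery |
| Pain input at session start (2.4) | not described | yes | no; used to adjust the treatment plan |
| ID entry at session end (2.4) | no | yes | no; verifies attendance |
| Visits at 8 weeks and 6 months (2.5, Table 2) | yes | yes | no |

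The formal route is common to both arms. The imbalance is the therapist contact in one arm only. The pain input could partly offset it, but pain change would not reveal a skin reaction.

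**2. Illustration of size**

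The protocol gives no adverse-effect rate and no capture rate, so it has no figure of its own to reproduce.

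- From section 2.7: n = 105 per arm.
- Assumed: the same true risk p in both arms (5%, 10% or 20%).
- Assumed: capture c_F = 0.95 face-to-face, and c_T = 0.40, 0.60 or 0.80 at home.

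Formulas: expected recorded patients = 105 × p × c. The observed risk ratio is (p × c_T)/(p × c_F) = c_T/c_F, whatever p is. The chance of a false result is the sum of the two binomial probabilities over all pairs of counts in which a two-sided 5% Fisher exact test is significant with telerehabilitation lower.

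Worked case, p = 0.20: face-to-face 105 × 0.20 × 0.95 = 19.95. Telerehabilitation at 40% capture is 105 × 0.20 × 0.40 = 8.4; at 60% it is 12.6; at 80% it is 16.8.

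| True risk | Home capture | Expected recorded, face-to-face vs telerehabilitation | Observed risk ratio | Falsely lower in telerehabilitation |
|---|---|---|---|---|
| 5% | 40% | 5.0 vs 2.1 | 0.42 | 9% |
| 5% | 60% | 5.0 vs 3.2 | 0.63 | 4% |
| 5% | 80% | 5.0 vs 4.2 | 0.84 | 2% |
| 10% | 40% | 10.0 vs 4.2 | 0.42 | 27% |
| 10% | 60% | 10.0 vs 6.3 | 0.63 | 10% |
| 10% | 80% | 10.0 vs 8.4 | 0.84 | 3.5% |
| 20% | 40% | 20.0 vs 8.4 | 0.42 | 58% |
| 20% | 60% | 20.0 vs 12.6 | 0.63 | 23% |
| 20% | 80% | 20.0 vs 16.8 | 0.84 | 6% |

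**3. After the fix**

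With equal capture in both arms the expected risk ratio is 1.0. At 95% in each arm, the chance of a falsely lower result for telerehabilitation is 1.0–1.7% over the same true risks.

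**The case against.** A reader might infer that the protocol sets up two routes: in-person detection for the face-to-face arm, and phone or email for telerehabilitation. The text does not say that. The contact sentence covers all participants, the investigators' duty to record applies to both arms, and nowhere is it stated that therapists collect adverse effects at sessions. Detection by the therapist is an inference from the mode of delivery. It is a reasonable one, but it is not the protocol's procedure.

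A reader might also infer that the comparison is biased by a known amount. That is not supported either. No event or capture rate is given, and the shared visits and per-session pain input may narrow the gap. With 80% home capture, or a true rate of 5%, the chance of a false difference is below 10% throughout and often much lower. The protocol calls both treatments safe and well tolerated, so low rates are plausible.

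An article condenses the full protocol, and a common adverse-effect form may exist there. The absence of a form or of a Table 2 row would not by itself be a finding. Adverse effects are also not among the outcomes in 2.6, and no safety test is specified. All this limits the weight of the point. What stands is that the article commits to a between-arm comparison and describes unequal contact, and no contact it describes applies one solicited question to both arms.

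The reasoning in 2.9 about a monitoring committee is a separate matter. It does not alter this comparison and is not relied on here.

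**Conclusion.** The point holds as a risk of differential ascertainment, not as a demonstrated bias. The planned comparison of frequencies rests on voluntary reporting in both arms, plus regular therapist contact in one, for effects that are mild and brief. The probable direction is under-recording in telerehabilitation, making it look safer. That direction rests on the assumption that a therapist who is present learns of more such events than a patient at home volunteers.

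The size cannot be taken from the documents. It depends almost wholly on the capture gap: serious at 40–60% home capture with true rates of 10–20%, small at 80%. Safety is secondary in this economic evaluation, so the trial's main conclusions are not affected. The change is still worth making before recruitment proceeds far, because transient events that were never asked about cannot be recovered later.

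**What to change.** 1. Use one short, fixed set of questions in both arms at every session: skin reaction, muscle discomfort, any other new symptom, each yes or no with free text. Telerehabilitation patients answer on the existing session-end page beside the ID field; the therapist puts the same questions in the same words at each face-to-face session.
2. Repeat one solicited checklist, with the same recall period in both arms, at the 8-week and 6-month visits that all participants already attend, and add a row for it to Table 2.
3. State in 2.9 that the between-arm comparison uses these solicited data only, and that spontaneous reports by phone, email or in conversation are tabulated separately by arm.

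If the full protocol already contains such a common form, a sentence in 2.9 saying so would be enough.

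The cost is a few fields on an existing web page, a line on the session sheet, one checklist at existing visits, and about a minute per session. The downside is that more mild events will be recorded, particularly in telerehabilitation.

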### 2.6. Outcomes

The main outcome measure will be the healthcare resources used during the study, and their costs will be collected through questionnaires completed by the participants at baseline, post-treatment, and follow-up (6 months). Table 1 provides a detailed list of the relevant resource categories, the sources from which usage data are obtained, and the associated unit costs, Table 2 shows timepoints of assessments. The cost analysis will include resources and expenses related to primary and hospital care, diagnostic testing, and other direct out-of-pocket expenses incurred by the participants (e.g., transportation costs). In addition, the social costs associated with absenteeism and loss of productivity will be included as secondary outcomes. For each participant, information on their resource utilisation will be tracked by means of a receipt log. At each assessment, patients will be asked to recall and detail their use of the described resources during the preceding months. These data will then be converted into costs based on updated unit prices from official sources.

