### 2.8. Economic Evaluation

An economic analysis will be performed in STATA 19, including a CEA and a CUA, with the aim of estimating and comparing the incremental costs and benefits of the telerehabilitation and face-to-face care programmes. A six-month time horizon was chosen to capture not only the immediate effects of the interventions but also the costs and outcomes that arise during the months following their implementation. This duration allows a more comprehensive assessment of the interventions’ impact from a societal perspective. Missing cost data will be handled using appropriate techniques, such as multiple imputation, according to the type and magnitude of the missing data. We will use multiple imputation by chained equations. The imputation model will include all variables used in the CEA and CUA, assuming that data are missing at random. We will generate 20 imputed datasets, each analysed separately using the same statistical procedures. The results will then be pooled according to Rubin’s rules, providing unbiased estimates of variances that account for the uncertainty associated with imputed values. Given that the cost distribution is usually skewed due to the presence of patients with very high costs, the mean cost per patient will be presented together with confidence intervals obtained using non-parametric bootstrap methods [41]. QALYs will be calculated as the area under the curve connecting the utility scores recorded at baseline and at subsequent follow-up points. The results will be expressed as incremental cost-effectiveness ratios (ICERs), which reflect the additional cost per each additional unit of outcome achieved. An incremental analysis will be performed to calculate the difference in costs and the difference in outcomes (improvements in effectiveness measured in QALYs) associated with the telerehabilitation and face-to-face programmes. In order to address the uncertainty associated with sample variability, the joint distribution of the differences in costs and effects will be estimated through multiple simulations using non-parametric bootstrap methods. The simulated cost-effectiveness pairs will be graphically represented on a cost-effectiveness plane, and acceptability curves will be generated to reflect the probability that each alternative is cost-effective according to different willingness-to-pay thresholds per QALY [42]. In Spain, the value of a QALY is estimated to be between EUR 22,000 and EUR 25,000 [43]. A sensitivity analysis will be carried out to assess the robustness of the results against different values, assumptions, and methodological approaches [44]. As the time frame of this study is limited, it will not be necessary to apply discounting to costs or benefits. The economic analysis will be reported in accordance with the guidelines of the Consolidated Health Economic Evaluation Reporting Standards (CHEERS) [45].

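### Section 2.9 withdraws participants with severe adverse effects from the study without keeping cost and utility collection going, so their post-event data are lost to the economic comparison

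*Protocol article*

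**What the plan says.** The rule is in section 2.9: "In the event of severe adverse effects, the participant will be withdrawn from the study and referred to the pertinent medical unit". The same section defines adverse events as unwanted signs, symptoms or conditions after the intervention, "regardless of whether there is a direct causal relationship with the treatment". It justifies having no external data monitoring committee partly by the expected rarity: "Due to the very low risk of severe adverse effects".

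The data that the rule affects are described in three places.

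- Section 2.6: "The main outcome measure will be the healthcare resources used during the study", together with the costs. Participants keep a receipt log and are asked at each assessment to recall the resources used since the last one. Section 2.5 has them attend in person for this at baseline, at the end of the eight-week programme and at the six-month follow-up.
- Section 2.8 on utilities: "QALYs will be calculated as the area under the curve connecting the utility scores recorded at baseline and at subsequent follow-up points".
- Section 2.8 on missing data: multiple imputation by chained equations with 20 datasets. The model contains the variables of the cost-effectiveness and cost-utility analyses, "assuming that data are missing at random". Adverse events are not named as a variable in it.

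No section says that questionnaires, receipt logs or utility measurements continue after a withdrawal under section 2.9.

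**The concern.** In an economic evaluation, the resources used after a severe event and the accompanying loss of utility are part of the outcome. Emergency visits, referrals, diagnostic tests and medicines are all cost lines in Table 1. The rule stops measurement when such costs may be arising, so whether data are missing depends on something related to the outcome.

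The way the data are collected adds to the loss. Resource use is recalled at visits, so a participant withdrawn during the eight weeks would give no questionnaire after baseline. One withdrawn between the post-treatment and six-month visits would lose the whole interval since the post-treatment visit, including the cost of the event itself. The receipt log might hold part of this, but the article does not say that it is collected at withdrawal.

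If more participants are lost in this way in one arm than in the other, the cost difference and the QALY difference are both distorted in that arm's favour. Section 2.8 recognises that single participants can matter for mean costs: "Given that the cost distribution is usually skewed due to the presence of patients with very high costs". It says this to justify bootstrap intervals and does not connect those patients with adverse events.

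**Working it through.** The plan gives no figure on this point, so there is none to reproduce. The check has two parts.

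**1. Can the planned imputation recover the lost values?**

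- If the rule is followed, every participant with a severe adverse effect leaves the study. No participant with such an event then has later cost or utility data.
- The imputation model is fitted to observed values, so the later values of withdrawn participants are drawn from participants without such an event.
- Adding an adverse-event indicator would help little, because no observed outcomes exist for those who carry the indicator.
- Missing at random therefore cannot be expected to hold for these participants. Only observed data would fill the gap.

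**2. How large could the effect be?**

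Inputs from section 2.7: 105 participants per arm, planned cost difference EUR 300, standard deviation of cost EUR 600. Input from section 2.8: EUR 22,000 to EUR 25,000 per QALY. The documents give no rate or cost of severe effects, so the number of participants lost (k) and the excess counted cost of each (C) are assumptions.

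Let m be the mean cost of the other participants in the arm. With one participant at m + C observed, the arm mean is (104m + m + C)/105 = m + C/105. If that participant is omitted or imputed at m, the arm mean is m. In general the understatement is k × C / 105.

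- k = 1, C = EUR 2,000: 2,000/105 = EUR 19, which is 19/300 = 6% of the planned difference.
- k = 1, total cost EUR 5,000 against an assumed typical cost of EUR 600, so C = EUR 4,400: 4,400/105 = EUR 42, or 14%.
- k = 1, total cost EUR 10,000 on the same assumption, so C = EUR 9,400: 9,400/105 = EUR 90, or 30%.

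The EUR 600 typical cost is an assumption; in section 2.7 that figure is only the standard deviation. The last case is extreme, since 9,400/600 is almost 16 planned standard deviations. For scale, the planned standard error of the cost difference is 600 × √(2/105) = EUR 83.

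For QALYs, assume a utility loss of 0.2 for six months, which is 0.2 × 0.5 = 0.1 QALY. One participant shifts the arm mean by 0.1/105 = 0.00095 QALY. At EUR 22,000 to EUR 25,000 per QALY this is worth EUR 21 to EUR 24 per participant.

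With no severe events, or with equal losses in both arms, the bias in the difference is nil.

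**The case against.** The case against giving this much weight has several parts.

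- **The participants are not necessarily removed.** A reader might infer that they drop out of the cost and QALY comparison. The article does not say so. Section 2.8 plans multiple imputation, no section excludes withdrawn participants from the analysis, and data collected before withdrawal remain. What is lost is their observed data after the event. This objection stands.
- **The trigger may be narrow.** A reader might infer that any severe event, whatever its cause, leads to withdrawal. The causality-free definition is given for adverse *events*, whereas the rule speaks of adverse *effects*, a word that the section uses elsewhere for reactions to the electrodes or the exercises. The section does not separate the terms, so the broad reading is possible but not established.
- **Some costs would not be counted anyway.** Section 2.7 registers sick leave only when it is due to neck pain. Table 1 has no line for inpatient stays, although section 2.6 mentions hospital care in general. Full follow-up would therefore not capture every cost of an unrelated event. This stands, and it is why the illustration is confined to counted cost.
- **The size is hypothetical.** No rate or cost of severe effects is documented, and both arms receive the same exercises and electroanalgesia. That those affected would have the highest costs and lowest utilities is plausible but is not stated anywhere. One possible source of imbalance is that telerehabilitation is self-administered while the other arm is treated by therapists, so events might be detected differently. That too is inference.
- **An article condenses the full protocol.** The analysis population may well be defined elsewhere, and its absence here is not the point. The withdrawal rule, however, is stated outright, and following it as written loses the data.

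**Conclusion.** The point holds in a limited form. As written, section 2.9 ends study participation after a severe adverse effect, and the article provides for no further cost or utility collection. In a trial whose main outcome is resource use and cost, this loses relevant observed data that the planned imputation cannot be expected to restore.

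The expected impact is small. It depends on at least one severe effect occurring, on losses that differ between arms, and on the event's costs falling within the plan's cost categories. Under the assumption of one such participant in one arm and none in the other, the shift in mean cost is about EUR 19 to EUR 90, or 6% to 30% of the planned EUR 300 difference. These are illustrations and not estimates. The documents support neither a claim that the results will be materially biased nor a claim that the affected participants are excluded from the comparison. The change is worth making because it corrects a stated rule at very little cost.

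**What to change.** Two sentences are needed.

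- **Section 2.9:** state that, whatever is decided clinically about study treatment, the participant stays in the study for the scheduled cost and utility assessments unless he or she withdraws consent to follow-up. The referral to a medical unit is not affected. The same edit should say whether the rule concerns all severe adverse events or only effects of the treatment, so that the two terms in the section agree.
- **Section 2.8:** state that these participants are analysed in the arm to which they were randomised using their observed data, including the costs of the event that fall within the plan's cost categories.

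The assessments are already scheduled for every participant, so no new visits are required. If recruitment has begun, the change goes through the notification route that section 3 describes for protocol changes.
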